### Who will be included in each analysis {27b}

All enrolled patients with complete paired measurements will be included. Analysis for Objective 1 will be at the lesion level (up to 150 lesions from 50 participants). For Objective 2, the usability and implementation outcome analyses will include all providers who completed the relevant questionnaires. The cost analysis will include all patients enrolled during the study period.

### How missing data will be handled in the analysis {27c}

For Objective 1, if a measurement cannot be completed for a particular lesion using one method (e.g., SS3D cannot image a lesion on a highly curved surface), that lesion will be excluded from the paired analysis for that method. We will report the proportion and reasons for missing measurements. Given the cross-sectional, single-visit design, we anticipate minimal missing data. No imputation is planned for Objective 1. For Objective 2, if a provider does not complete a questionnaire, available data will be analyzed and the extent of missing data reported. For the cost analysis, missing cost elements will be estimated using median values from the available data at the same site.

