### Intervention and comparator

#### Intervention and comparator description {15a}

##### Intervention (SkinScan3D):

SS3D is a portable, handheld 3D imaging device manufactured by Pensievision. It uses a photon recording device combined with active optics capable of rapid change of focus, thereby achieving one-click, all-focus, 3D imaging using only a single perspective. The device consists of a custom-designed light ring (enabling white- and colored-light imaging), an electronically controlled liquid lens (Corning Varioptic A-16F0), an 8-megapixel camera, and a Raspberry Pi 4 Model B microcomputer with a 6-inch touchscreen display, all housed in a polycarbonate enclosure. A cup-shaped front-end adaptor ensures fixed shooting angle, camera-to-skin distance, and controlled illumination. A 73-frame image set requiring 8-9 seconds to collect is processed by AI software to generate a 3D map. The device provides automated measurements of lesion area, height, volume, and color. It operates on an internal lithium battery without requiring electricity or internet connectivity. The disposable front-end adaptor is the only consumable component. For each participant, five 3D snapshots of each of three target lesions are collected.

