### Outcomes {16}

#### Objective 1 (Reproducibility and Accuracy)

##### Primary outcomes:

(1) Concordance correlation coefficient (CCC) for inter-rater reproducibility of KS lesion area measurement. The CCC will be calculated separately for SS3D and for the ruler-based method, based on measurements by two independent clinicians of the same three lesions per participant. The measurement variable is projected lesion area (mm^2^). The method with the higher CCC will be considered the more reproducible. (2) Coefficient of determination (R-squared) for each measurement method, assessing the proportion of variation attributable to true lesion size versus random measurement error.

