### Statistical methods

Statistical methods for primary and secondary outcomes {27a}

#### Objective 1

We will plot a graph for each measurement method. Each graph’s x-axis will represent measurements from clinician 1 and y-axis will represent measurements from clinician 2. For each graph, we will calculate the concordance correlation coefficient (CCC) and coefficient of determination (R-squared). The CCC measures reproducibility (agreement) between clinicians for each method. The method with the higher CCC will be considered the more reproducible, and the method with R-squared closer to 1 will be considered the more accurate. We will also visualize agreement between methods graphically using Bland-Altman plots, and report the mean difference and 95% limits of agreement. To provide a more robust assessment, we will also report mean absolute error and root mean square error to capture the magnitude of differences between methods.

#### Objective 2

System Usability Scale (SUS) scores will be computed following standard scoring procedures (score contributions from items summed and multiplied by 2.5, yielding a score range of 0 to 100). Device usability will further be normalized to generate percentile ranks and graded as either acceptable (score above 68), marginal, or not acceptable. AIM, IAM, and FIM scores will be presented as means, standard deviations, and ranges. Qualitative data collected from semi-structured interviews will be transcribed, coded, and thematically analyzed to identify sub-themes and themes related to SkinScan3D implementation in routine clinical settings. Data triangulation will be applied to cross-validate findings from interviews and direct observation to ensure rigor and validity of the qualitative analysis.

For the cost analysis, we will summarize data to estimate the total program cost of SS3D per patient and per visit, excluding research costs. Costs will be broken down by the categories in Table 2 to identify key cost drivers.

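### The missing-measurement rule lets the SS3D and ruler statistics rest on different lesions, so the primary comparison can be biased in either direction

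*Protocol article*

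**What the plan says.** For Objective 1, two clinicians measure three lesions per participant with both methods, giving at most 150 lesions from 50 participants. Under Outcomes {16}, "The CCC will be calculated separately for SS3D and for the ruler-based method". Section {27a} plots clinician 1 against clinician 2 for each method and takes a CCC and an R-squared from each plot. It then applies a ranking rule: "The method with the higher CCC will be considered the more reproducible". The R-squared nearer to 1 identifies the more accurate method.

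Section {27c} covers a lesion that one method cannot measure. Its example is that "SS3D cannot image a lesion on a highly curved surface", and its rule is that "that lesion will be excluded from the paired analysis for that method". It adds "No imputation is planned for Objective 1", promises to report how many measurements are missing and why, and expects few.

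Section {27b} defines the analysis population: "All enrolled patients with complete paired measurements will be included". It does not say what the pair is. The Discussion counts measuring the same lesions with both methods as a strength of the design, because it controls for patient-level variation.

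**The concern.** Since {27a} forms one clinician-against-clinician plot per method, the paired analysis for a method is most naturally that method's two-clinician pairs. A lesion that SS3D cannot image then leaves the SS3D CCC and R-squared but stays in the ruler's. A ruler failure would work the other way.

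Both statistics depend on the lesions they are computed on as well as on the method. They fall when the set contains lesions that are hard to measure, and they fall when the spread of lesion sizes narrows. Two methods with identical measurement error can therefore differ simply because one was assessed on a different set. Failure is unlikely to be unrelated to the lesion, as the protocol's own example is a feature of the lesion's location.

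At stake is the primary conclusion of Objective 1. The winner is whichever point estimate is higher, so a small artefact is enough to decide it, and the same-lesion comparison that the Discussion relies on is lost for every failed lesion.

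**Working it through.** **1. The plan's own precision figures.** Table 1 is reproduced by the Fisher z interval tanh(atanh(CCC) ± 1.96/√(n − 3)), treating lesions as independent. At n = 150, 1.96/√147 = 0.162. For CCC 0.8 this gives 0.734 to 0.851 (stated 0.73 to 0.85). For CCC 0.9 it gives 0.864 to 0.927 (stated 0.86 to 0.93). All six cells agree to two decimals.

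**2. Effect of difficulty, by formula.** Let V be the between-lesion variance, E the error variance, f the share of hard lesions and m the multiplier on their error SD. With no systematic difference between clinicians, in large samples

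CCC = V / (V + E[1 + f(m² − 1)]).

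Take V = 0.90 and E = 0.10, so ordinary lesions have CCC 0.90. If hard lesions are unrelated to size, are dropped from SS3D and are kept for the ruler, SS3D stays at 0.90. With m = 2 the ruler falls to:
- f = 5%: 0.90/1.015 = 0.887
- f = 10%: 0.90/1.03 = 0.874
- f = 20%: 0.90/1.06 = 0.849

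In this model R-squared is the square of the CCC in large samples. At f = 10% the R-squared gap is therefore 0.81 − 0.764 = 0.046.

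**3. Effect of which lesions are lost, by simulation.** There were 3,000 replicates of 50 participants with 3 lesions each, with two methods of identical true error. From the protocol: 150 lesions, and planning CCCs of 0.8 and 0.9. Assumed: within-participant correlation 0.3; failure rates 5%, 10% and 20% (8, 15 and 30 lesions); and the error multipliers. Failed lesions leave the SS3D set only. Cells show mean SS3D CCC minus ruler CCC, then the share of replicates in which SS3D ranks higher; 50% is the fair value.

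| Failed lesions | Base CCC | 5% | 10% | 20% |
|---|---|---|---|---|
| Unrelated to size, no harder | 0.8 | −0.001 (50%) | 0.000 (50%) | −0.001 (50%) |
| Unrelated to size, error SD ×1.5 | 0.9 | +0.006 (62%) | +0.011 (72%) | +0.022 (85%) |
| Unrelated to size, error SD ×2 | 0.9 | +0.014 (77%) | +0.027 (89%) | +0.051 (98%) |
| Unrelated to size, error SD ×2 | 0.8 | +0.026 (75%) | +0.044 (86%) | +0.085 (97%) |
| Mostly the largest, no harder | 0.9 | −0.017 (19%) | −0.027 (10%) | −0.044 (3%) |
| Mostly the largest, no harder | 0.8 | −0.031 (20%) | −0.046 (12%) | −0.074 (5%) |
| Mostly the largest, error SD ×2 | 0.8 | −0.004 (46%) | 0.000 (49%) | +0.013 (60%) |

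The negative rows arise because removing large lesions shrinks V, which lowers the SS3D CCC although its error is unchanged.

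**4. After restricting both methods to the common set.** The mean CCCs agree to within 0.002 and SS3D ranks higher in 47% to 53% of replicates in every scenario, so the artefact disappears. Precision barely changes. With 135 common lesions the interval is 0.730 to 0.854 at CCC 0.8 and 0.862 to 0.928 at CCC 0.9. With 120 it is 0.725 to 0.856 and 0.859 to 0.929.

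**The case against.** The strongest reply is that the effect may be negligible. The protocol expects few missing measurements, promises to report their number and reasons, and describes the study as exploratory. At 5% failure and doubled error the shift is 0.014 at CCC 0.9, less than half the half-width of the Table 1 interval, (0.927 − 0.864)/2 = 0.032. This stands as a limit on size. It does not dispose of the point: the ranking uses no interval or margin, and reporting failures shows the imbalance without removing it. Nor can the rule be left to a later plan, since section {5} says the statistical analysis plan is contained in {27a} to {27d}.

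Three stronger readings are tempting, and the document does not support them.

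- **That the rule tilts the comparison towards SS3D.** The rule is worded for either method; SS3D on a curved surface is only its example. A tilt towards SS3D requires that the failed lesions also be hard to measure by ruler. That is plausible for curved surfaces but stated nowhere, and loss of large lesions pushes the other way.
- **That {27b} contradicts {27c}.** If the pair in {27b} is the two clinicians, the sections agree. If it is the two methods, {27b} already supplies a common set and {27c} departs from it. The fault is an undefined word.
- **That SS3D is favoured by repeated readings.** The intervention description says "five 3D snapshots of each of three target lesions are collected". But no section says the five are averaged, and none says the ruler is read only once. If averaging is the intended use of the device, it is part of the method being tested. This point does not rest on it.

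**Conclusion.** The concern holds in a limited form. As written, {27c} allows the two primary CCCs, and likewise the two R-squared values, to be computed on different lesions and then ranked by point estimate. The resulting bias can favour either method or be absent.

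For equal methods, the shift is about +0.014 to +0.051 towards SS3D at CCC 0.9, if 5% to 20% of lesions fail and those lesions double the error SD of both methods. It is about −0.03 to −0.07, towards the ruler, at CCC 0.8 if the failures are mainly large lesions that are no harder to measure. It is near zero if failures are unrelated to both size and difficulty. The protocol gives no failure rate, so all of these rest on assumed rates and error multipliers, and few failures mean a small effect. The point merits correction because the remedy removes the artefact whatever its direction and costs almost no precision. It is not evidence that the study is biased towards the device.

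**What to change.** In {27b} and {27c}:

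1. Define the primary comparison of CCC and R-squared on the common set: lesions with all four readings, that is, both clinicians by both methods.
2. State in {27b} that a complete paired measurement means exactly this, so that the two sections use one definition.
3. Report each method's CCC on all lesions available for that method as a sensitivity analysis, beside the proportion and reasons for failure already promised.

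This changes wording only and needs no new data or visits. Trial status shows that Uganda began recruiting on 1 April 2026, so the change should be recorded before any Objective 1 measurements are compared. The downside is that a few usable readings, mostly ruler readings if SS3D fails more often, leave the primary set. The main comparison then describes lesions that both methods can measure, which is why the failure proportion must be reported next to it.

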##### Secondary outcomes:

(1) Acceptability of Intervention Measure (AIM), Intervention Appropriateness Measure (IAM), and Feasibility of Intervention Measure (FIM) scores.^12^ (2) Time-and-motion data characterizing clinic workflows, task-shifting, and time associated with clinic visits. (3) Implementation cost per patient and per visit, estimated using activity-based micro-costing.^13^

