### Sample size {19}

Objective 1: Assuming that the mean and variance of the area of lesions (as determined by the SkinScan3D method) are the same for two clinicians, then the expected width of a 95% confidence interval (CI) for the concordance correlation coefficient for a given number of lesions examined is shown in Table 1. Therefore, with at least 50 participants with 3 lesions each (150 lesions), we will get a precise estimate of the CCC. To address overinterpretation of the concordance, we will complement the R-squared with additional metrics that capture accuracy more directly, including Bland-Altman plots to assess agreement and systematic bias, mean absolute error, and root mean square error. These measures will allow us to evaluate both correlation and the magnitude and direction of differences between methods.

Objective 2: We will roll out the refined SS3D intervention to 100 participants (50 patients at UCI; 25 at JOOTRH; 25 at Homa Bay). All providers will complete quantitative surveys. We anticipate recruiting providers (up to n=10), clinic administrators and key decision makers (up to n=5) who will participate in semi-structured interviews at each clinic. The final sample of semi-structured interviews will be determined by the point at which thematic saturation is achieved.

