## Figures and Tables

**Figure 1 F1:**
[figure not shown]
Manual bidimensional measurement for Kaposi sarcoma skin lesions using the AIDS Clinical Trial Group (ACTG) method (not drawn to scale). Three representative morphologies are shown: (A) oval, (B) round, and (C) irregular. Lesion area is calculated as the product of thelongest diameter (d_1_) and the longest perpendicular diameter (d_2_), both measured in millimeters using a ruler. This method does not capture lesion height, volume, or color.

**Table 1. T2:** Expected width of 95% confidence intervals (precision)

Number of lesions	CCC = 0.8	CCC = 0.9
50	0.67 to 0.88	0.83 to 0.94
100	0.72 to 0.86	0.85 to 0.93
150	0.73 to 0.85	0.86 to 0.93

**Table 2. T3:** Summary of cost measures and associated data sources

Cost type	Elements	Data sources
**Start-up**	Training materials; training expenses (trainer fees, staff time spent in training)	Project expense reports; staff/civil service salaries
**Implementation**	Training expenses; technical assistance; fidelity monitoring; community outreach	Project expense reports
**Personnel**	Time/salaries of healthcare personnel, supervisors, and administrative staff	Direct observations; salaries; interviews
**Patient**	Transportation; other out-of-pocket expenses including childcare; time losses	Patient surveys; local average wages
**Supplies**	Consumables utilized or dispensed on a per-patient basis, particularly front-end adaptors	Clinic and project expense reports
**Capital**	SkinScan3D equipment utilized in clinics	Manufacturing and shipping costs
**Utilities**	Space/storage, internet, electricity, other overhead costs associated with SS3D	Clinic and project expense reports

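### Filling missing cost elements with the site median does not preserve the mean cost being estimated, and can distort the patient-cost category in either direction

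*Protocol article*

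**What the plan says.** Section {27c} of the protocol article fixes a single-imputation rule for the Objective 2 cost analysis: "missing cost elements will be estimated using median values from the available data at the same site". Section {5} states that the analysis plan is contained in {27a} to {27d}, so this is the operative rule and not a placeholder.

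The quantity to be estimated is in {27a}, where data are summarised to "estimate the total program cost of SS3D per patient and per visit, excluding research costs". It is also the third secondary outcome of Objective 2 in {16}: "Implementation cost per patient and per visit, estimated using activity-based micro-costing". The population in {27b} is everyone: "The cost analysis will include all patients enrolled during the study period". A breakdown is planned too: "Costs will be broken down by the categories in Table 2 to identify key cost drivers".

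Table 2 mixes two kinds of element. The patient row lists "Transportation; other out-of-pocket expenses including childcare; time losses", taken from patient surveys and local average wages. Other rows, such as capital ("SkinScan3D equipment utilized in clinics"), come from project, clinic or manufacturer records.

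**The concern.** A total divided by the number of patients or visits is a mean. To leave a mean undistorted, the filled-in values must average to the mean of the missing ones. A median does so only where median and mean coincide. Costs bounded at zero with a few large values usually have a median below the mean. An element that most patients do not incur has a median of zero.

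The rule also says nothing about what a blank is. A blank childcare entry may be an unanswered question or a cost that did not arise, and the two call for different treatment.

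At stake are a stated secondary outcome and, more directly, the ranking of cost categories used to name the cost drivers. Patient costs rest on surveys, where gaps are plausible, so an error that falls mainly on this category shifts its apparent share.

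**Working it through.** The protocol gives no cost, SD, skewness or expected missing fraction, so there is no figure to reproduce. Every distribution and missing fraction below is an assumption. Site sizes (50, 25 and 25 patients) come from {19}.

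**1. Element incurred by every patient.** Let *m* be the fraction missing completely at random. Observed values contribute (1 − *m*) × mean and filled values *m* × median, so

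relative bias = *m* × (median/mean − 1).

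For a log-normal cost with log-SD *s*, median/mean = exp(−*s*²/2).

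| *s* | median/mean | bias, *m* = 20% | bias, *m* = 30% |
|---|---|---|---|
| 0.5 | exp(−0.125) = 0.882 | −2.4% | −3.5% |
| 1.0 | exp(−0.5) = 0.607 | −7.9% | −11.8% |

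In terms of the coefficient of variation, median/mean = 1/√(1 + CV²), which is 0.894, 0.707 and 0.555 for CV 0.5, 1 and 1.5. The bias is then −1.1%, −2.9% and −4.5% at *m* = 10%, and −2.1%, −5.9% and −8.9% at *m* = 20%.

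**2. Element incurred by fewer than half of patients, zeros recorded.** The median is 0, so the formula gives −*m*. A simulation (20,000 replicates, 25 or 50 patients per site, 30% incurring the cost, CV 0.5 to 1.5) gave −11.3% to −12.2% at 12% missing and −19.1% to −20.1% at 20% missing. Across all simulated settings, filling with the site mean left a bias within ±0.5%.

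**3. Blanks that are really zeros.** Let a fraction *p* incur the cost and suppose everyone else leaves the item blank. Then *m* = 1 − *p*, and the observed values are all positive. Taking the mean among those who incur the cost as 1,

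relative bias = (1 − *p*) × median / *p*.

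- *p* = 0.7: 0.3 × 0.894/0.7 = +38% (CV 0.5); 0.3 × 0.555/0.7 = +24% (CV 1.5).
- *p* = 0.3: 0.7 × 0.894/0.3 = +209% (CV 0.5); 0.7 × 0.555/0.3 = +130% (CV 1.5).

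If only half of the non-incurrers leave a blank, the overstatement at *p* = 0.7 is +9% to +17%. At *p* = 0.3 it is 0, because the observed median is then zero and happens to be the right fill.

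**4. Dilution into total cost.** Suppose skewed elements that every patient incurs make up 20% to 80% of total cost (an assumption), with *m* = 10% to 20% and CV 0.5 to 1.5. The total is then low by between 0.2 × 0.10 × (1 − 0.894) = 0.2% and 0.8 × 0.20 × (1 − 0.555) = 7.1%.

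**The case against.** A reader might infer that the rule biases SS3D cost low and so makes the device look cheaper. The documents do not support that:

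- A downward bias needs right skew, values missing completely at random, costs not incurred recorded as zero, and a non-trivial missing fraction. The protocol states none of these. Step 3 of the working shows the direction reversing when blanks are true zeros, and a symmetric element has no bias.
- The argument reaches mainly the patient row of Table 2 and possibly observed staff time. Start-up, implementation, capital and utilities come mostly from project, clinic or manufacturing records and have little or no patient-level distribution within a site. If local average wages are used to value lost time, part of the skew disappears. Childcare sits inside a wider out-of-pocket item and may not be imputed on its own.
- Section {27a} describes SS3D cost and plans no cost contrast with the ruler. In such a contrast, elements common to both periods would be handled by the same rule.

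All of this stands. It is also fair that this is a descriptive secondary outcome in an exploratory study, and that a median resists a single extreme value at sites with 25 patients. None of it restores the match between rule and target: a robust summary of a typical patient is not what a total per patient requires. The possibility of reversal is a further reason to define what a blank means.

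**Conclusion.** The concern holds in a limited form. The imputation rule in {27c} is mismatched to the mean cost defined in {27a}. Under log-normal costs missing completely at random, a right-skewed patient-level element is understated by about 2% to 8% at 20% missing for log-SD 0.5 to 1.0. A rarely incurred element with recorded zeros is understated by about its full missing fraction. If blanks stand for costs not incurred, the element can be overstated instead, in some settings heavily. The effect on overall cost is diluted by site-level elements (0.2% to 7.1% low under the shares assumed in step 4, for elements that every patient incurs), and neither its size nor its direction can be settled from the document. The practical risk is a distorted patient category in the cost-driver breakdown. This is a modest point, worth making because the correction is cheap.

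**What to change.** In {27c}, replace the median rule with three statements:

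1. A cost that was not incurred is recorded and analysed as zero, separately from a missing value. This must come first, because a site mean would also put a positive cost in place of a true zero.
2. Patient- and visit-level elements that are truly missing are imputed with the mean for the same site and period, or by multiple imputation using site and period. Period belongs in the rule because {18} has cost data collected in both the ruler and the SS3D periods, and conditioning on site alone leaves it open whether an SS3D-period gap is filled from ruler-period values.
3. A complete-case cost is reported as a sensitivity analysis.

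This takes a few lines of text and no new study data, provided the cost forms let staff enter an explicit zero. The price is that a mean is more sensitive to one extreme value, which matters most at the two sites with 25 patients. Comparison with the complete-case result gives a partial check.
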